### Statistical analyses

The study will determine if the provision of PrEP to 2,600 people at high risk of HIV infection in Victoria results in a 30% decline in new HIV infections among GBM over the 36 months of the study. In addition, the study will monitor the rate of new HIV infections in Victoria for a period of 36 months after the PrEPX study commences. Analyses of changes in the rates of HIV infection will be undertaken using Mann-Whitney U and chi-square tests to determine whether there has been a significant decline in new HIV infections during this 36-month period, compared to the 36 months prior to PrEPX commencing.

We will undertake further analyses to determine whether or not other factors such as an increase in background HIV and STI testing rates during the PrEPX study period and an increase in the background rate of HIV virological suppression of HIV positive people living in Victoria during the PrEPX study period may have contributed to any decrease in new HIV infections. These analyses will be undertaken using Cox proportional and logistic regression analyses to calculate hazard or rate ratios and odds ratios, respectively, with 95% confidence intervals. To determine the factors associated with incident HIV infection among trial participants, we will explore demographic and behavioral risk factors.

To answer the study secondary aims a range of datasets and analyses will be employed, as required. The enrolment survey, ACCESS behavioral survey, and ACCESS test data will be used to explore baseline demographics, behavior, HIV risk factors, prevalence of STIs and blood borne viruses among GBM presenting for PrEP, changes in behavior and STI rates among PrEP users and ancillary health benefits among PrEP users. The in-depth online survey and interviews will be used to explore attitudes to PrEP, reasons for taking PrEP and attitudes around sexual behavior since the availability of PrEP. We will use ACCESS test data, pharmacy data and in-depth online surveys to explore PrEP adherence. Monthly aggregate data from the state NPEP service will be descriptively analyzed to explore state wide use of clinic survey and ACCESS test data will be used to explore the capacity of study clinics to prescribe PrEP.

All statistical analyses will be performed using Stata version 14 (StataCorp LP, College Station, Texas, USA) with a significance cut off of *p* = 0.05.

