PrEP is currently registered for use in Australia, and will be listed on the national list of medicines [the Pharmaceutical Benefits Scheme (PBS)] on 01 April 2018. In 2016, three pharmaceutical companies had their co-formulated tenofovir and emtricitabine products approved by Australia's Therapeutic Goods Administration (TGA) for use in HIV prevention (21–23). In Australia, medicines listed on the PBS cost $39 AUD or $7 AUD for person eligible for concession (24) per dispensed medication, but because PrEP is not currently subsidized through the PBS obtaining PrEP via a private prescription incurs costs up to $900 AUD per month (25, 26). Generic PrEP can be imported from overseas through the TGA personal importation scheme, wherein registered medical practitioners provide individuals with clinical monitoring and 3-monthly prescriptions for PrEP (27). The cost of personally importing PrEP ranges between $70–230 USD (approximately $90–300 AUD) for a 3 month supply (28, 29); delays in customs and shipping have been reported (30). Finally, PrEP can be accessed through jurisdiction-level PrEP implementation projects, which either provide participants free study medication, or require that participants pay costs commensurate with current PBS prices. Six of the eight Australian jurisdictions offer PrEP via population intervention studies, with the size and number of studies increasing significantly since the first PrEP demonstration project, VicPrEP, began enrolment in Victoria in June 2014 (Table 1) (17, 31–36). VicPrEP demonstrated that PrEP could be successfully prescribed and managed in general practice in Victoria, providing preliminary evidence for the current, larger demonstration study, PrEPX (17).

**Table 1 T1:** PrEPX study timeline, 2013–2019.

**Phase**	**Date**	**Activity**
Pre-PrEPX	2013–2014	Community advocacy for PrEP access and forums held by VAC to discuss PrEP, PrEP stigma and future clinical trials.
	Jun 2014–Dec 2016	VicPrEP study−30 month demonstration project enrolled 114 participants across four sites in Melbourne.
	Jun–Aug 2015	PrEP'D for Change and PrEPaccessNOW formed. General practitioners developed guidelines for prescribing off-label PrEP.
	Dec 2015	Victorian PrEP Accord was signed. Signatories include VAC, LPV, PrEP'DforChange, PrEPaccessNOW, time4PrEp, VicPrEP.

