PrEPX planning	Sep-Dec 2015	Approached clinics and community pharmacies to participate in the PrEPX study. Approached peak organizations including VAC, LPV, VACCHO, Centre for Culture, Ethnicity and Health.
	29 Jan 2016	Funding announced by the Victorian DHHS, Alfred Health and VAC for 2,600 places in PrEPX study.
	30 Jan 2016	Study registration opened using REDCap on the Alfred hospital website. Data collected: name, contact details, preferred clinic to attend for PrEPX, whether participant was on PrEP.
	22 Jul 2016	2049 people registered interest on online formClinics provided with partially de-identified list from registration form to enable workforce planning when study openedRegistered individuals emailed about study opening dates and booking information for their preferred clinic.
PrEPX study period	26 Jul 2016	PrEPX enrolment began (wave one of study enrolment) 2600 places opened, 150 of these reserved for priority populations including people who inject drugs and/or people in serodiscordant heterosexual partnerships with high or medium risk for HIV acquisition as per PrEP prescribing guidelines (Table 2).
	14 Oct 2016	PrEPX study neared enrolment capacityStudy enrolment stopped at 2200 participants to allow for people who had booked an appointment and not yet attended to join the study, with other places reserved for priority populations.First waitlist was opened, pending further funding.
	17 Jan 2017	Additional 600 places in PrEPX announced, funded by VAC.
	19 Jan 2017	Additional places released (wave two of study enrolment)All 575 people registered on the waitlist were provided a study place. Clinics were provided a list of participants as per original PrEP enrolment.
	20 Jan 2017	Waitlist was reopened.
	28 Mar 2017	Additional 600 places announced, funded by Victorian DHHS.
	29 Mar 2017	Additional places released (wave three study enrolment)All 617 people registered on the waitlist were provided a study place Clinics were provided list of participants as per original PrEP enrolment.
	30 Mar 2017	Waitlist was reopenedWaitlist remains open November 27th 2017.
	30 June 2019	PrEP-X study estimated end date.

*VicPrEP, Victorian PrEP demonstration study; PrEPX, Victorian PrEP population level study; PrEPX-SA, expansion of PrEPX study to South Australia; VAC, Victorian AIDS Council, LPV, Living Positive Victoria; VACCHO, Victorian Aboriginal Community Controlled Health Organisation Inc.; DHHS, Department of Health and Human Services*.

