### Data collection

#### Registration and waitlist data collection

When study funding was announced in January 2016, a database (study registry) was established so that individuals could register their interest in the study thereby assisting the study team's plans for study implementation (Table 1). The register collects participants' contact details, previous PrEP use and which study site participants would prefer to attend.

A few days prior to commencement of study enrolment, registered individuals were emailed information on how to book a PrEPX appointment at their preferred study site and information on whether co-payment would likely be required by the clinic at study enrolment. Clinics were provided with a list of individuals planning to attend their clinic, including contact details, if currently using PrEP and if currently a client at that clinic.

The study opened on 26 July 2016 and data collection among enrolled participants is scheduled until July 2019.

As enrolment neared capacity (*n* = 2,600) a waitlist register was established so individuals could register their interest if further places became available. The waitlist register collected the same variables as the initial registry of interest. Consistent with the protocol at study opening, with each release of additional study places registered individuals were emailed details of their preferred study site and clinics were emailed information on their potential PrEPX participants.

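### About 15 to 16 of the 36 post-start months follow the 1 April 2018 PBS listing, so a pooled decline cannot be credited to the PrEPX study places

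*Protocol article*

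**What the plan says.** Under Study aims, the protocol article ties the primary question to a fixed intervention: PrEP for 36 months to 2,600 people, with target declines of 30% in gay and bisexual men (GBM) and 25% state wide. The Abstract frames the same question around up to 3,800 people. The argument below does not depend on which number is used.

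The Statistical analyses section sets the window: "the study will monitor the rate of new HIV infections in Victoria for a period of 36 months after the PrEPX study commences". The reference is historical, "compared to the 36 months prior to PrEPX commencing", and the method is unadjusted: "Analyses of changes in the rates of HIV infection will be undertaken using Mann-Whitney U and chi-square tests". No split, change point or concurrent comparison is given for this analysis.

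On dates, "The study opened on 26 July 2016 and data collection among enrolled participants is scheduled until July 2019". Table 1 gives 30 June 2019 as the "PrEP-X study estimated end date". The Introduction says that PrEP "will be listed on the national list of medicines [the Pharmaceutical Benefits Scheme (PBS)] on 01 April 2018".

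Further analyses will look at "other factors such as an increase in background HIV and STI testing rates during the PrEPX study period" and at "an increase in the background rate of HIV virological suppression of HIV positive people living in Victoria during the PrEPX study period". The limitations in the Discussion mention PBS listing only when considering how closely the study resembles routine conditions.

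**The concern.** The listing date was known to the authors and falls inside the post-period. Before listing, the Introduction puts private prescription at up to $900 AUD a month and personal importation at roughly $90 to $300 AUD for three months. After listing, the patient pays $39 or $7 AUD per dispensing. More people outside the study are likely to start PrEP, and any infections they avoid lower the same state-wide notification count that the primary comparison uses.

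Table 1 shows demand beyond the funded places. Waitlists of 575 and 617 people filled before each extra release, and a further waitlist was still open in November 2017.

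At stake is the causal statement. The 2,600 figure was derived in order to avert a stated number of infections, and planners would read the result as what that many places achieve. If part of the fall comes from PrEP supplied outside the study, the effect per place is overstated by an amount that the planned analysis cannot reveal.

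**Working it through.** **The plan's own chain.** From Sample size estimates:
- GBM at risk: 225 / 0.0078 = 28,846. High-risk GBM: 28,846 × 0.24 = 6,923.
- Target: 0.30 × 225 = 67.5, stated as 68 infections averted per year.
- 2,600 × 0.0278 = 72.3 per year at full effectiveness. The target therefore implies an effectiveness of 68 / 72.3 = 0.94. The article does not state this value; it is back-solved here.

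**Overlap with listing** (months of 30.4375 days):

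| Period | Days | Months |
|---|---|---|
| 26 July 2016 to 1 April 2018 | 614 | 20.2 |
| 1 April 2018 to 26 July 2019 (36 months from start) | 481 | 15.8 |
| 1 April 2018 to 30 June 2019 (Table 1 end date) | 455 | 14.9 |

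Shares after listing: 481 / 1,095 = 44%; 455 / 1,069 = 43%. These are shares of calendar time, not of effect.

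**Possible size of the misattribution.** Non-study uptake is not in the document. Assume X net additional high-risk users, all starting at listing, with incidence 2.78 per 100 person-years and effectiveness 0.94. Averaged over the 36 months, infections averted per year = X × 0.0278 × 0.94 × 0.439.

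| Assumed X | Averted per year | Share of 67.5 | Points of decline on 225 |
|---|---|---|---|
| 500 | 5.7 | 9% | 2.6 |
| 1,000 | 11.5 | 17% | 5.1 |
| 2,000 | 23.0 | 34% | 10.2 |

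For scale, 6,923 − 3,800 = 3,123 estimated high-risk GBM would remain outside the study even if every place went to that group.

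**Precision if the window is split.** Take the document's 225 GBM infections per year and a constant 30% decline, with SE(log RR) = √(1/pre + 1/post). The 36 pre-months give 675 cases, and the post-period rate is 157.5 per year.

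| Post-period | Cases | SE | RR (95% CI) |
|---|---|---|---|
| Full 36 months | 472.5 | 0.060 | 0.70 (0.62 to 0.79) |
| Pre-listing, 20.2 months | about 265 | 0.073 | 0.70 (0.61 to 0.81) |
| Post-listing, 15.8 months | about 207 | 0.079 | 0.70 (0.60 to 0.82) |

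These intervals are optimistic. They assume Poisson counts, the full effect from the first day, and diagnoses that track infections without delay.

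**The case against.** - **The co-factor list is open.** It is introduced by way of example, ACCESS extracts prescriptions and its survey records previous PrEP use, and the Discussion plans to triangulate notifications with ACCESS data. So non-study PrEP is not excluded, and the material to study it partly exists. But nothing plans for it, and the article does fix the window, comparator and tests.
- **The test itself is not invalid.** It can still show whether notifications fell. That stands; what weakens is the attribution.
- **Listing is not the start of non-study PrEP.** A reader might infer that listing opens PrEP to everyone. The Introduction describes a subsidy with a co-payment and says that importation and private prescription already existed. Listing is a step up, so even the pre-listing segment does not isolate PrEPX.
- **Truncating to 20 months is not a clean remedy.** The aim specifies 36 months of provision. Under Study setting, only 148 of 286 diagnoses in 2015 were newly acquired; the other 138 (48%) lacked evidence of infection within 12 months. Diagnoses of infections that predate the study would weigh most on the early months and pull an early-only estimate towards the null. This stands, and is why the 36-month comparison should be kept.
- **Slow enrolment is a minor issue.** A reader might infer that the early months were barely exposed. Table 1 shows enrolment paused at 2,200 on 14 October 2016, 80 days after opening: 85% of 2,600, or 58% of 3,800.
- **Participants moving to PBS supply** does not by itself change how many people take PrEP, so it does not inflate the decline.

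**Conclusion.** The concern holds as an attribution problem. The stated aim credits a decline to a fixed number of study places, while 43% to 44% of the post-period follows subsidised access outside the study and no planned analysis separates the two. The dates come from the article and the overlap is simple arithmetic.

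The size of the bias is unknown. The range of 9% to 34% of the target rests on an assumed 500 to 2,000 extra users, a back-solved effectiveness of 0.94, immediate uptake at listing and the high-risk incidence figure. A reader might infer that 44% of any observed effect is spurious; the documents do not support that. Earlier non-study use also matters: if it grew between the two 36-month periods, it too would add to the apparent decline.

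If the aim were restated as the effect of all PrEP availability in Victoria, the overlap would matter much less. As written, it is not.

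**What to change.** Keep the 36-month monitoring and the before-after comparison, and make these changes before analysis:

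1. Analyse monthly notification rates with a change point at study opening and a second at 1 April 2018, for example by Poisson or negative binomial regression. Report the pre-listing and post-listing periods separately, alongside the pooled result.
2. Add PrEP obtained outside the study (importation, private prescription and, after listing, PBS supply) to the named co-factors, with its data source. ACCESS prescriptions and survey items are a starting point, limited to the participating clinics.
3. State that the post-listing and pooled 36-month estimates reflect all PrEP in Victoria, and that only the pre-listing estimate bears mainly on PrEPX.
4. Give preference to newly acquired diagnoses if the notification data allow it. Notifications include test history, but the fields named for extraction under Other study data do not include it or newly acquired status, so the request may need extending.

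No new data are needed for the split, because the line-listed notifications already carry diagnosis dates. The costs are wider intervals per segment (0.61 to 0.81 and 0.60 to 0.82, against 0.62 to 0.79 pooled, under the assumptions above) and a pre-listing estimate that may be diluted towards the null by enrolment build-up and by infections acquired before the study. Restricting to newly acquired diagnoses would roughly halve the counts on the 2015 split (148 of 286).

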### Study aims

In Victoria, three quarters of new HIV diagnoses are among GBM and the knowledge of, interest and willingness to use PrEP is high amongst GBM at higher risk of HIV acquisition (37). We hypothesize that the provision of PrEP to individuals at high risk of HIV would be both justified and feasible and could achieve a population level reduction in HIV incidence. The primary aim of this study is to determine if the provision of PrEP for 36 months to 2,600 people at high risk of HIV infection in Victoria will result in a 30% decline in new HIV infections in GBM and a 25% state wide decline in new HIV infections.

The study's secondary aims are to explore:
Baseline demographics, behavior, HIV risk factors, prevalence of STIs and blood borne viruses among GBM presenting for PrEP.Attitudes to PrEP, reasons for taking PrEP and attitudes around sexual behavior since the availability of PrEP.PrEP adherence.Changes in sexual behavior and STI rates among PrEP users.Use of non-occupation post exposure prophylaxis (NPEP) in Victoria.The capacity of study clinics to prescribe PrEP.Any ancillary health outcomes associated with PrEPX participation.

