#### Other study data

Clinic staff at three of the four Victorian primary care clinics, two sexual health clinics, and the hospital clinic have been invited to complete a survey about characteristics of their clinic, their PrEP patient load and clinic level challenges experienced during the study at baseline, months 12 and 24.

Pharmacy data including drug accountability logs and participant record logs are manually collected from each participating site.

Victorian HIV diagnosis data will be collected from the Victorian Department of Health and Human Services (DHHS). It is a legal requirement that all newly diagnosed cases of HIV are notified to the DHHS. Notifications include test result data from the laboratory and an enhanced surveillance form from the diagnosing doctor that includes demographics, test history and exposure to HIV. Non-identifiable line listed data will be collected from the Victorian DHHS including the diagnosis date, country of birth, age, and exposure to HIV for all newly diagnosed cases in Victoria between 2013-2019.

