### Sample size estimates

We estimated that there are 300 new HIV infections per year in Victoria based on back-calculation methods applied to surveillance data and a modeling framework. With high and stable testing rates and HIV notification trends in Australia, these estimates have demonstrated strong concordance with actual trends in new infections (1, 48, 49). Approximately 75% of new HIV infections in Victoria occur in GBM, providing an estimate that 225 new infections occur in GBM in Victoria, annually.

We powered the study to avert 68 new HIV infections annually among GBM, which equates to a 30% reduction in new HIV infections in GBM in Victoria. We consider that this would represent a meaningful population-level prevention outcome from scaling up PrEP. Power calculations were based on a HIV incidence estimate of 2.78 per 100 person years (PY) from high risk GBM (consistent with risk criteria guidelines for PrEP) in the Health in Men (HIM) cohort study (50). The HIM study measured HIV incidence among GBM in Sydney in the early-to-mid 2000s (50). There are not adequate, contemporary Victorian data to determine HIV infection risk for GBM, but participants in HIM were not dissimilar in characteristics nor in epidemiological context to GBM in Victoria and Wilson et. al. has shown that the per-capita transmission rate has remained relatively stable since that period (51). We estimated that the number of GBM at risk of HIV in Victoria was 28,846 (225/0.78 per 100PY). With an estimated 24% classified as high risk [as per the HIM study (50)] and hence targeted for study participation, our target population size was therefore estimated as 6,923 (28,846 × 0.24). We estimated that a sample size of 2,600 participants (37% of high risk GBM) was required to achieve the 30% annual HIV infection reduction outlined above. Achieving this PrEP coverage was considered feasible given recent survey data showing that 32% of GBM classified as having high HIV acquisition risk were both willing and eligible to use PrEP (37).

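### The only tests named for the primary before/after comparison give no estimate to set against the 30% and 25% targets and make no allowance for a background trend

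*Protocol article*

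**What the plan says.** Under Study aims, the primary aim is to determine whether providing PrEP "will result in a 30% decline in new HIV infections in GBM and a 25% state wide decline in new HIV infections". Statistical analyses repeats the 30% GBM target. It then describes the analysis of infection rates as "undertaken using Mann-Whitney U and chi-square tests to determine whether there has been a significant decline in new HIV infections during this 36-month period". The reference period is the 36 months before the study began, and all analyses are run "with a significance cut off of *p* = 0.05".

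The same section then commits to further analyses of whether rising background HIV and STI testing, or rising virological suppression, contributed to any decrease: "These analyses will be undertaken using Cox proportional and logistic regression analyses to calculate hazard or rate ratios and odds ratios". It names no dataset for these models and does not say that they adjust the primary comparison.

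For the outcome, Other study data says: "Non-identifiable line listed data will be collected from the Victorian DHHS". The list covers all newly diagnosed cases in 2013-2019 and includes the diagnosis date and the HIV exposure category.

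**The concern.** The question is about size and cause: did PrEP provision produce a fall of 30% (GBM) or 25% (state)? The tests answer something narrower: do the 36 months after differ from the 36 months before? Two things follow.

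- **Size.** A p-value cannot be compared with 30% or 25%. A significant result is compatible with a fall far short of either.
- **Cause.** Pooling each 36-month block removes calendar time. A decline already under way, or starting for another reason, enters the comparison in full.

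The article itself gives reasons not to take a flat background for granted. Statistical analyses names testing and viral suppression as rival explanations. Study setting records subsidised antiretrovirals at any CD4 count since 2013. The Introduction gives a subsidy listing for PrEP of 1 April 2018, which leaves about 15 months of the study window with PrEP available outside the study. Table 1 shows places released in waves from July 2016 to March 2017, so the intervention itself was phased in.

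**Working it through.** **Inputs.** Sample size estimates gives 300 new infections a year in Victoria, 75% of them in GBM. The significance level is 0.05; two-sided is assumed, since the article does not say. Monthly counts are taken as Poisson. Background decline rates and ramp lengths below are assumptions; the article gives none.

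**Plan's own figures.** 300 × 0.75 = 225 GBM infections a year; 225 × 0.30 = 67.5, which the plan rounds to 68. Over 36 months, GBM 225 × 3 = 675 and state 300 × 3 = 900.

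**Smallest significant fall.** For two equal periods with counts A (before) and B (after), chi-square = (A − B)² / (A + B), with critical value 3.841.

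- GBM: 675 to 604 gives 71² / 1279 = 3.94 (significant); 605 gives 70² / 1280 = 3.83 (not). 71 / 675 = 10.5%.
- State: 900 to 818 gives 82² / 1718 = 3.91 (significant); 819 gives 81² / 1719 = 3.82 (not). 82 / 900 = 9.1%.

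**What the same totals could give.** With SE of the log rate ratio = √(1/A + 1/B), a fall from 675 to 472.5 is a 30% decline with a 95% interval of about 21-38%. A fall from 900 to 675 is 25%, interval about 17-32%. Both remain unadjusted for trend.

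**Background decline with no PrEP effect.** Each month after lies 36 months later than its counterpart before, so a fall of r per year gives a before/after ratio of (1 − r)³. The chance of a significant decline is about 1 − Φ(1.96 − z), where z = (A − B) / √(A + B). For GBM at r = 3%: B = 675 × 0.9127 = 616.0, z = 59.0 / 35.9 = 1.64, chance 37%.

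| Assumed fall per year | Before/after fall | GBM, chi-square | State, chi-square |
|---|---|---|---|
| 0% | 0% | 2.5% | 2.5% |
| 1% | 3.0% | 8% | 9% |
| 2% | 5.9% | 19% | 24% |
| 3% | 8.7% | 37% | 47% |
| 5% | 14.3% | 78% | 88% |

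Simulation agrees with the GBM column to within about 3 percentage points. Mann-Whitney on monthly counts behaves alike (GBM about 35% at 3% per year and 73% at 5%). A background fall of 11.2% per year alone gives 1 − 0.888³ = 30%.

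**A trend-adjusted alternative.** Simulated Poisson regression of 72 monthly GBM counts with a linear trend, true full effect 30%, no background decline:

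| Roll-out of the effect | Step term: power, mean rate ratio | Matching ramp term: power, mean rate ratio |
|---|---|---|
| Immediate | 85%, 0.70 | same model |
| 6-month ramp | 62%, 0.77 | 78%, 0.70 |
| 9-month ramp | 43%, 0.81 | 74%, 0.71 |
| 12-month ramp | 31%, 0.84 | 75%, 0.69 |

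With a 5% per year background fall, the ramp-term powers are 70-75%. With no PrEP effect, false declines stay at about 2-3%. For the 9-month ramp the SE of the log rate ratio is about 0.136, so an estimate of 0.70 would carry an interval of 0.70 × exp(±1.96 × 0.136), about 0.54 to 0.91.

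**The case against.** The plan is more careful than its two tests suggest, and several stronger readings go too far.

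- **A reader might infer that any background decline will be credited to PrEPX.** The article does not support this. It commits to examining testing and virological suppression, and the Discussion admits that diagnoses are only a proxy for incidence and plans triangulation with ACCESS data. What stands is that these analyses are not linked to the primary comparison and do not cover a general secular trend.
- **A reader might infer that the Cox and logistic models are unusable.** They cannot be fitted to a list of cases alone, which has no non-cases and no risk sets. But the article does not say they will be. ACCESS holds individual longitudinal test results, on which such models are feasible.
- **A reader might infer that the decline cannot be estimated.** The totals yield a crude rate ratio with an interval, as shown above, and a condensed article may leave that to the analysis plan. Nor does the article say that p < 0.05 would prove 30%. What stands is that the tests it does name for the primary question return neither.
- **A reader might take the bias as certain.** The Introduction reports national notifications stable over four years, and Sample size estimates refers to stable testing and notification trends. With no trend, the false-decline rate is nominal. Past stability does not, however, guarantee a flat background through 2019.

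**Conclusion.** The point holds and should be settled before the primary analysis. As named, the comparison can be significant at a third of the GBM target (10.5% against 30%) and at little more than a third of the state target (9.1% against 25%), and it cannot separate PrEPX from a secular change. These thresholds follow from the plan's own case numbers with Poisson counts. The false-decline rates also depend on the assumed background falls: negligible excess at 0%, modest at 1%, serious from about 3% per year. The documents establish that the design is exposed to this bias, not that it will occur.

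**What to change.** 1. Make the primary analysis a Poisson or negative-binomial regression of monthly notifications, separately for GBM and the state. Include a calendar trend anchored in the pre-period, a phased PrEPX term (monthly number on PrEPX, or a ramp fixed in advance) and autocorrelation-robust standard errors. Avoid an instantaneous step: under a 9-12 month ramp it has only about 30-50% power across simulation runs and understates the effect.
2. Report the rate ratio with 95% interval at full roll-out and set it against 0.70 (GBM) and 0.75 (state).
3. Enter background testing and viral suppression as sensitivity covariates in this model. Exclude tests that PrEPX itself mandates each quarter, since these are a consequence of the intervention.
4. Keep Mann-Whitney and chi-square as descriptive. Keep Cox and logistic models for individual-level data, and name the dataset.
5. State that the model assumes the earlier trend would have continued, and that it does not by itself separate study PrEP from PrEP obtained elsewhere after the April 2018 listing.

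Cost: analysis-plan wording and modest programming. Dated notifications for 2013-2019 are already to be collected, so no new outcome data are needed. The real price is precision: wider intervals, and power for a true 30% effect falling from about 100% to roughly 70-85%, depending on the ramp.
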